## Abstract

By involving a multidisciplinary team, the model creates a holistic care pathway that supports the medical, psychological, and social needs of adolescents and their caregivers during the transition process. Epilepsy is a prevalent neurological disorder in childhood, and many childhood-onset epilepsy cases persist into adulthood, necessitating a transition from pediatric to adult care. This transition requires a structured process to address medical and psychosocial l needs; however, many epilepsy centers lack formal programs to support this transition, and there is a need for a standardized approach to ensure that patients and their families are adequately prepared. Therefore, we developed the Epi-STEP protocol, a multidisciplinary transition model for young adults with epilepsy and their caregivers. This monocentric observational study will assess the potential usefulness of the transition process for patients with epilepsy aged 16 and older, recruited from the Child Neuropsychiatry Unit at the IRCCS Mondino Foundation. Data will be collected at three time points: at the last visit at the Child Neuropsychiatry Unit (T0), at the first visit at the Adult Epileptology Service (T1), and at a 12-month follow-up (T2). Assessment tools will include both standardized instruments and ad-hoc questionnaires specifically developed to comprehensively evaluate the transition process and will be completed by patients, caregivers, and healthcare professionals. This study will evaluate the utilityof the transition process, assessing readiness for adult care and psychosocial well-being of the patients involved. Findings will guide targeted interventions to improve clinical outcomes, enhance transition readiness, and provide better support for patients and families during this critical phase. Finally, this model designed for epilepsy could be further adapted to other chronic conditions requiring structured transition regimens.

**Trial registration:**

The study has been registered at ClinicalTrials.gov (registration number NCT06778772) on the 16th January 2025.

**Specifications table**

**Table utbl0001:** 

**Subject area**	*Neuroscience*
**More specific subject area**	Medicine, psychology
**Name of your protocol**	Epi-STEP: A Multidisciplinary Transition Model for Patients with Epilepsy
**Reagents/tools**	Not applicable
**Experimental design**	Monocentric observational study with an approximal duration of 48 months. Data will be collected at three time points: on the last visit at the Child Neuropsychiatry Unit (T0), on the first evaluation at the Adult Epileptology Service (T1) and on a 12-month follow-up appointment (T2).
**Trial registration**	The study has been registered at ClinicalTrials.gov (registration number NCT06778772) on the 16th January 2025.
**Ethics**	Prior participation to the study, informed consent will be obtained by patients and by their caregivers. If patients are under 18 years old, consent will be obtained by their legal guardian.
**Value of the Protocol**	By involving a multidisciplinary team, the model creates a holistic care pathway that supports the medical, psychological, and social needs of adolescents and their caregivers during the transition process. This model designed for epilepsy could be further adapted to other chronic conditions requiring structured transition regimens

## Background

Epilepsy is a neurological disease characterized by an enduring predisposition to generate epileptic seizures and often carries neurobiological, cognitive, psychological, and social consequences [1]. It is a common neurological condition in childhood, with an incidence of 5–7 cases per 10,000 children and adolescents [2]. Many childhood-onset epilepsy cases do not achieve remission in adulthood [3], thus necessitating a transfer from pediatric to adult epileptology [4]. This transfer, however, goes beyond a simple "handover" of care; it involves a well-coordinated process addressing the medical, psychosocial, and psychoeducational needs of patients with epilepsy (PWE) and their families [5].

Transition is a structured process that supports adolescents and young adults with chronic conditions in moving from child-centered to adult-oriented healthcare systems, ensuring continuity of care while addressing medical and psychosocial needs. Unlike the transfer of care, which represents a single event, transition is a gradual and dynamic process requiring preparation, patient engagement, and coordination between healthcare providers. The primary aim of the transition process is to minimise the risk of clinical deterioration, suboptimal treatment adherence, and loss to follow-up, all of which may substantially compromise the quality of life of patients and their families [6]. Well-organized transition pathways have been associated with improved long-term outcomes and better patient engagement. When inadequately managed, this phase may lead to poor adherence and loss to follow-up, with potential negative consequences on clinical outcomes [5].

Despite the necessity of a holistic transition process has been recognized, it is still challenging to apply and maintain effective transition programs, and it is only in recent times that shared operational models have emerged as viable solutions [[7], [8], [9], [10]]. Currently, many specialized epilepsy centers lack structured programs designed to support a transition process that adequately addresses the diverse needs of both PWEs and their families. Often, pediatric and adult care teams work independently, making collaboration difficult: while pediatric care emphasizes developmental and psychosocial factors with holistic, family-centered approach, adult care tends to focus more on disease management, with an emphasis on clinical treatments. This shift can pose significant challenges for those with psychiatric comorbidities, cognitive impairments, or specialized care requirements [5].

At the Pediatric and Adolescent Epilepsy Center of IRCCS Mondino Foundation (Pavia, Italy), 15-18% patients are over the age of 14 and present complex, drug-resistant epilepsy, often accompanied by neuropsychiatric comorbidities. To address these needs, we developed an integrated transition service that fosters collaboration between pediatric and adult neurologists. To further systematize this approach, we developed EPI-STEP (Support, Transition, Education, and Pathways for patients with EPIlepsy), a structured and replicable transition program organized into three main phases: (T0) multidisciplinary assessment at the Child Neuropsychiatry Unit, (T1) joint transition visit with pediatric and adult care teams, and (T2) follow-up after transfer to adult services. The program is supported by standardized assessment tools and the involvement of a dedicated transition coordinator, while allowing care to be tailored to the individual clinical, psychological, and social needs of each patient.The EPI-STEP model, validated within a transition protocol approved by the local Ethics Committee, provides a structured framework to support the transition of PWE from pediatric to adult care. The primary objective is to assess transition readiness in patients and their caregivers, reflecting their preparedness to assume responsibility for healthcare management, treatment adherence, and communication with clinicians during the transition process. Secondary objectives include the evaluation of health-related quality of life (HRQoL) and behavioral and emotional functioning, as well as the identification of unmet clinical and psychosocial needs potentially affecting transition readiness. The protocol further explores patient and caregiver experiences of the transition process, including perceived adequacy of information, expectations regarding adult care, and concerns related to continuity and autonomy. Collectively, these measures aim to provide a multidimensional characterization of factors associated with transition readiness and to inform the development of an individualized transition pathway to adult epileptology services.

## Description of protocol

This is a monocentric observational study approved by our local Ethics Committee (approval code 2023–3.11/173) and registered at https://clinicaltrials.gov (code NCT06778772) on 16th January 2025. Prior participation, patients and caregivers will be fully informed about the study procedure and will be required to sign a written informed consent.

### Participants

Participants will be recruited by the Child Neuropsychiatry Unit of the IRCCS Mondino Foundation. Inclusion criteria are as follows: a) being at least 16 years old b) clinical diagnosis of epilepsy of any aetiology, for which a clinical follow-up over time is expected.

Exclusion criteria are: a) Patients who don’t receive the indication to continue the epileptological follow-up after their last visit at the Child Neuropsychiatry Unit; b) caregivers/patients who choose not to continue follow-up care at our center.

#### Sample size calculation

Being the primary outcome purely descriptive, it is not possible to calculate the required sample size. At the Pediatric and Adolescent Epilepsy Center of IRCCS C. Mondino, which follows approximately 900 patients annually, 13% are over the age of 16, satisfying the inclusion criteria. Considering a maximum of 25% of subjects that don’t give the consent to the participation, we planned to enroll a minimum of 90 participants. With the sample planned, considering a percentage of readiness expected of 70%, with a confidence level of 0.95 we can reach a precision of the estimate of 9%.

### Procedures

The estimated total duration of the study is 48 months, of which 36 months will be employed in participants’ recruitment and minimum follow-ups will be organized after 12 months.

To evaluate the effectiveness of the transition process for both PWEs and their caregivers, data will be collected on the last visit at the Child Neuropsychiatry Unit (T0), on the first evaluation at the Adult Epileptology Service (T1) - usually between 6 and 18 months depending on the clinical needs of the PWEs - and on a 12-month follow-up appointment (T2). Study data will be collected in pseudo-anonymised form in an appropriate Case Report Forms (CRF; see Supplementary material 1), designed ad hoc and developed in compliance with good clinical practice (GCP) guidelines.

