#### T0- therapeutical, clinical, psychiatric and neuropsychological re-evaluation

The evaluation at the time of the study enrollment (T0) will be conducted either in-patient or in outpatient regimen, based on the clinical complexity of the participant’s condition and certainty of diagnosis.

The diagnostic and therapeutic re-evaluation will be carried out at the Child Neuropsychiatry facility. Specifically, transition package will comprise:- anamnestic interview.- therapeutic reassessment.- re-evaluation of the diagnosis, including EEG, brain MRI, metabolic and genetic tests, if necessary.- psychodiagnostic and neuropsychological assessment through standardized tests and clinical interviews (for detail please refer to “Measure” paragraph).

The diagnostic framework and therapeutic indications formulated by the pediatric neurologist will be shared with the general practitioner and adult neurologist, through a “Transition Passport” (see Supplementary material 2), in order to update them and to ensure the involvement of these crucial professionals in the follow-up and future care of the patients.

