#### T2-Follow-up transition appointment

Around 12 months (T2) after the first transition assessment, the PWEs/caregivers are further interviewed in person or by telephone regarding their transfer experience.

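### The stated 48-month duration leaves no time for the usual 6 to 18 months between T0 and T1, so it does not fit the protocol's own visit schedule

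*Protocol article*

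**What the plan says.** The protocol article gives all the parts of the timeline.

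- **Total duration.** The Specifications table describes a "Monocentric observational study with an approximal duration of 48 months". The Procedures section repeats the total: "The estimated total duration of the study is 48 months, of which 36 months will be employed in" recruitment. It then sets the minimum follow-up at 12 months.
- **Enrolment.** The T0 section ties study entry to the last paediatric evaluation: "The evaluation at the time of the study enrollment (T0) will be conducted" as an inpatient or outpatient.
- **T0 to T1.** The Procedures section places the first adult evaluation "usually between 6 and 18 months depending on the clinical needs of the PWEs".
- **T1 to T2.** The T2 section places the follow-up interview "Around 12 months (T2) after the first transition assessment", and the preceding section heading identifies that assessment as T1.

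The Statistical analysis section evaluates the primary outcome (ETRC) across T0, T1 and T2. It reports the proportion ready at each timepoint, and applies repeated measures ANOVA and three pairwise comparisons. Under Measures, the adult behavioural instruments (ASR, ABCL) are collected at T2 only.

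**The concern.** The total is the sum of recruitment and one 12-month follow-up. The schedule, however, has two intervals after enrolment, and the 12 months cover only the second. A participant who enters late in recruitment cannot complete the schedule within the stated duration.

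At stake is the T2 data. The T2 readiness proportion, two of the three pairwise ETRC comparisons and the whole behavioural comparison need it. Repeated measures ANOVA in its standard form also drops anyone without T2. If collection did end at month 48, the loss would not be random: the T0-to-T1 interval depends on clinical needs, so participants with longer intervals would be under-represented at T2.

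**Working it through.** **Inputs.** Total 48 months, recruitment 36 months, T0-to-T1 interval L usually 6 to 18 months (Procedures); enrolment at T0 (T0 section); T2 about 12 months after T1 (T2 section); minimum of 90 participants and 70% expected ready, with a stated precision of 9% (Sample size calculation).

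**Step 1: reproduce the stated duration.** 36 + 12 = 48 months. This matches exactly and leaves 0 months for L.

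**Step 2: time needed per participant.** L + 12 = 18 to 30 months after T0.

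**Step 3: last participant.** With T0 in month 36, T2 falls in month 36 + L + 12, which is 54, 60 or 66 for L = 6, 12 or 18.

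**Step 4: latest T0 that still allows T2 by month 48.** T0 ≤ 48 − 12 − L = 36 − L, which is month 30, 24 or 18. Steps 1 to 4 need no accrual assumption.

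**Step 5: share without T2.** This assumes collection stops at month 48 and accrual is uniform over 36 months. The share is then L/36. The half-width is 1.96 × √(0.70 × 0.30 / n). At n = 90 it is 9.5 points, which is the right comparator for the stated 9.

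| L (months) | Share without T2 | Of 90, with T2 | 95% half-width at 70% |
|---|---|---|---|
| 6 | 6/36 = 17% | 75 | 10.4 points |
| 12 | 12/36 = 33% | 60 | 11.6 points |
| 18 | 18/36 = 50% | 45 | 13.4 points |

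With L uniform on 6 to 18 months, the average loss is 12/36 = 33% (simulation: 33.3%). No dropout is included.

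**Step 6: sensitivity to accrual shape.** Averaged over L uniform on 6 to 18 months, the loss is about 12% if accrual is linearly front-loaded and about 55% if linearly back-loaded.

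**Step 7: T1.** T1 is reached by month 48 if T0 ≤ 48 − L. That fails for nobody at L = 6 or 12, and for 6/36 = 17% at L = 18. The average loss is about 4% under uniform accrual and uniform L, so the problem is mainly one of T2.

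**The case against.** A reader might infer that about one third of participants cannot reach T2. The documents do not support that as a fact. It needs uniform accrual over the full 36 months, a mean interval of 12 months and a hard stop at month 48, and the article states none of these.

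- **Accrual may be faster.** The sample size section describes a pool of 900 × 13% = 117 patients, of whom 117 × 75% ≈ 88 would consent. That is close to the planned 90, which is itself a minimum. If 90 enrolled within 18 months, all would reach T2 by month 48 even at the longest usual interval (18 + 18 + 12 = 48). With uniform accrual over 24 months and L uniform on 6 to 18, about 6% would miss it. If recruitment runs the full 36 months, the total could exceed 90 and the counts above would have the wrong denominator. The accrual rate is not given, so neither pattern is established.
- **Month 48 may not be a cut-off.** The duration is called estimated or approximate, and nothing says that pending T2 contacts are abandoned. Selective loss at T2 is therefore a conditional consequence, not a feature of the plan as written.
- **The effect on precision is modest.** The stated 9% names no timepoint, and the like-for-like baseline is 9.5. In the central case the change is 11.6 − 9.5, about 2 points.

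These points limit the size and leave the inconsistency in place. An approximate total can absorb rounding, but here the sum is exact without an interval of 6 to 18 months. Counting T2 from T0 would rescue the 48 months, but the T2 section counts it from the first transition assessment, and with an 18-month interval T2 would then precede T1.

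**Conclusion.** The point holds as an inconsistency between the stated duration and the visit schedule. For the last enrolled participants the total falls short by 6 to 18 months, and anyone enrolled after month 30 with a usual interval cannot reach T2 by month 48. That conclusion uses only the article's own figures, reading the 6 to 18 months as running from T0. The article does not name the starting point, but no other reading is sensible.

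The number of participants without T2 is conditional. It is 17% to 50% by interval if collection stops at month 48 and accrual is uniform, and roughly 12% to 55% on average for front- or back-loaded accrual. It could be zero if enrolment is fast or collection continues past month 48. A firm statement that one third will be lost, or that T2 results will be biased, goes beyond the documents.

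**What to change.** Define study end as T2 of the last enrolled participant, and restate the estimated total duration as about 54 to 66 months (36 + 6 to 18 + 12) in both the Specifications table and the Procedures section. The definition should lead, because the interval is only usually 6 to 18 months and so even 66 months does not guarantee T2 for everyone. The visit timings themselves need no change for this.

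If 48 months must stand, state the expected number with T2 as a range, name the accrual and interval assumptions behind it, and restate the T2 precision to match (for example 10.4 to 13.4 points for 75 to 45 participants). Closing recruitment at month 18 would also fit 48 months at the longest usual interval. It halves the recruitment period, though, and should not be adopted without showing that 90 can still be reached.

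The cost is an amendment to the stated duration, a check that the registry entry agrees, and either a later final report or a smaller stated T2 sample.

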#### T0- therapeutical, clinical, psychiatric and neuropsychological re-evaluation

The evaluation at the time of the study enrollment (T0) will be conducted either in-patient or in outpatient regimen, based on the clinical complexity of the participant’s condition and certainty of diagnosis.

The diagnostic and therapeutic re-evaluation will be carried out at the Child Neuropsychiatry facility. Specifically, transition package will comprise:- anamnestic interview.- therapeutic reassessment.- re-evaluation of the diagnosis, including EEG, brain MRI, metabolic and genetic tests, if necessary.- psychodiagnostic and neuropsychological assessment through standardized tests and clinical interviews (for detail please refer to “Measure” paragraph).

The diagnostic framework and therapeutic indications formulated by the pediatric neurologist will be shared with the general practitioner and adult neurologist, through a “Transition Passport” (see Supplementary material 2), in order to update them and to ensure the involvement of these crucial professionals in the follow-up and future care of the patients.

#### T1-First transition appointment

After reassessing the patient's clinical condition and confirming the indication for the transition process, the Epilepsy Nurse (Transition Coordinator) arranges the logistical details of the appointment (T1) at the Adult Neurology Service, ensuring the co-presence of both the pediatric and adult neurologists, and other healthcare practitioners, if needed.

#### T2-Follow-up transition appointment

Around 12 months (T2) after the first transition assessment, the PWEs/caregivers are further interviewed in person or by telephone regarding their transfer experience.

#### Measures

During the last evaluation at the Child Neuropsychiatry Unit (T0), subjects will complete the Italian version of the following tools:•Patient-Reported Questionnaires:- Epilepsy Transition Readiness Checklist (ETRC) [11]- Pediatric Quality of Life Inventory - Teen version (PedsQL 4.0) [12]- Youth Self-Report (YSR/11–18) [13]•Caregiver-Reported Questionnaires:- Child Behavior Checklist (CBCL/6–18) [14]- Caregiver versions of the ETRC and the PedsQL.•Pediatric Neurologist-Reported Questionnaire:- Screening Transition NEEDS Questionnaire (see Supplementary material3)

During appointments at the Adult Epileptology Service (T1 and T2), participants and caregivers will complete assessments as follows:•T1 Visit:- Participants and Caregivers: PedsQL, ETRC, and Qualitative EPI-STEP Questionnaire version A (see Supplementary material 4)•T2 Visit:- Participants and Caregivers: PedsQL, ETRC, Adult Behavior Checklist (ABCL) [13], Adult Self-Report (ASR) [13] and Qualitative Epi-STEP Questionnaire version B (see Supplementary material 4)

#### Assessment tools overview

**Screening Transition NEEDS Questionnaire** (see Supplementary material 3): to provide a comprehensive understanding of the factors influencing transition readiness and to identify potential barriers, the Screening Transition NEEDS Questionnaire was developed. This tool, grounded in clinical and theoretical literature, offers a systematic and practical method for evaluating the complex needs of patients transitioning from pediatric to adult epilepsy care. The clinician completes five subsequent items assessing five crucial domains in the transition process (diagnostic, therapeutic, social, educational and emotional issues). Each question from A1 to A5 is worth 20% in the case of a negative response (“No”), while a positive response (“Yes”) corresponds to a score of 0%. A higher score indicates a greater degree of readiness. A score of 100% indicates that there are no gaps and so that the patient is fully ready for the transition. The cut-off score on the questionnaire is set at 60%. If a patient scores below this threshold, it suggests that there are critical aspects that need to be addressed before proceeding with the transfer. During the clinical visit, if the clinician identifies significant deficiencies in any domain (scores between 60% and 80%), appropriate interventions or recommendations will be made to address those areas. For instance, if a patient is undergoing psychodiagnostic evaluation due to a psychiatric comorbidity, and this aspect is not yet resolved, the clinician may identify a gap in the psychological/emotional domain and decide to delay the transition. Similarly, if there has been a recent change in the therapeutic regimen that requires follow-up, the therapeutic domain may need further attention before transitioning to adult care. At the end of this evaluation, a final question (question B) assesses whether the clinician believes that the patient and their family are ready for the transfer to adult neurology. Question B has two response options, “Yes” or “No”. The former response represents 100%, indicating readiness for the transition, while the latter corresponds to 0%, meaning that there are gaps that still need to be addressed, resulting in a postponement of the transition.

**Qualitative Epi-STEP Questionnaire** (see Supplementary material 4): explores timing and introduction to the transition process, quality of information provided, expectations from adult neurology care and concerns about continuity of care and autonomy, with parallel patient and caregiver versions. This tool includes two versions: Version A, completed at T1, and Version B, completed at T2. Both assess the same domains, except that Version A is completed at the beginning of the transition process, while Version B is filled when the patient is already under the care of adult services and contains an additional question to assess the overall level of satisfaction with the transition process. This tool, grounded in clinical and theoretical literature, offers a systematic and practical method for evaluating the complex needs of patients transitioning from pediatric to adult epilepsy care.

**YSR/11–18** (Youth Self-Report) and **ASR** (Adult Self-Report): evaluate adaptive functioning, behavioral/emotional problems and social competencies, the former in teenagers, the latter in adults. Since participants are still under 18 at the beginning of the transition process, at T0 they complete the YSR/11–18, while at T2 they fill out the ASR.

**CBCL/6–18** (Child Behavior Checklist) **and ABCL** (Adult Behavior Checklist): caregiver reports providing insight into the individual's behavior and emotional state. The CBCL/6–18 is a parallel version of the YSR/11–18 and is given at T0, the ABCL is the parallel version of the ASR and is handed at T2.

**PedsQL** (Pediatric Quality of Life Inventory): assesses health-related quality of life (HRQoL) across physical, emotional, and social domains, with parallel patient and caregiver versions. According to the patient's age, the appropriate version will be administered, either the Teen (age 13–18) or the Young adult (age 18–25) version [12].

**ETRC** (Epilepsy Transition Readiness Checklist): explores the patient’s readiness for the transition process in 16–17-year-old teenagers, with parallel patient and caregiver versions. This checklist investigates to which extent the patient is capable and ready to manage healthcare issues, compliance to pharmacological therapy and communication with clinicians. These measures provide a structured framework for evaluating transition readiness and identifying barriers to successful transitions from pediatric to adult epilepsy care.

Patients should indicate the response that best applies to them on a 4-point Likert scale (0 = I don't know; 1 = No, but I am learning to do this; 2 = Yes, I have started doing this; 3 = Yes, I always do this), with a total score ranging from 0 to 72. A higher score indicates greater readiness.

For the caregiver version, questions 1 to 16 assess the caregiver's perception of the child's readiness using a 4-point Likert scale (0 =No, my child does not know this, 1= No, but my child is learning to do this, 2= Yes, my child has started doing this, 3= Yes, my child always does this), with a total score of 48. A higher score indicates a greater perception of readiness by the caregiver. For questions 17 to 25, which assess the parent's knowledge regarding the transition, the responses are based on a 4-point Likert scale (0 = No, I do not know 1 = I know some of this 2 = I know most of this 3 = I know all about this), with a total score ranging from 0 to 24. Higher scores indicate greater knowledge. The scoring system for the questionnaire, adapted for this study, is essential for assessing participants' readiness in a standardized and objective manner.

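### YSR/CBCL and ASR/ABCL are assigned by visit on the premise that everyone is under 18 at T0, but eligibility has no upper age limit, so some participants can receive a form meant for another age group

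*Protocol article*

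**What the plan says.** The Assessment tools overview describes the YSR as the form for teenagers and the ASR as the form for adults, and then assigns them by visit: "Since participants are still under 18 at the beginning of the transition process, at T0 they complete the" YSR/11–18, with the ASR at T2. The caregiver forms follow the same pattern, CBCL/6–18 at T0 and ABCL at T2. The Measures section repeats this assignment without any age condition.

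Other parts of the article describe the population differently:

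- Participants, inclusion: "a) being at least 16 years old b) clinical diagnosis of epilepsy of any aetiology". Neither exclusion criterion concerns age.
- Abstract: "patients with epilepsy aged 16 and older".
- Specifications table, Ethics: "If patients are under 18 years old, consent will be obtained by their legal guardian".

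For the PedsQL, the same overview selects the version by the patient's age, "either the Teen (age 13–18) or the Young adult (age 18–25) version". The Measures section, however, names only the Teen version at T0.

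Statistical analysis compares YSR/ASR and CBCL/ABCL between T0 and T2 with paired t-tests or non-parametric equivalents.

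**The concern.** The rule for choosing the form rests on a statement about age that the eligibility criteria do not enforce. If it is false for a participant at T0, that person completes a youth form when already past its age label. At T2 the rule assumes that everyone has become an adult, and the visit schedule does not guarantee this either.

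At stake is the secondary outcome on behavioural and emotional functioning. It is analysed as a within-person difference, so a form that does not suit the participant's age at either end affects that person's paired value. The choice of form cannot be changed once it has been completed.

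**Working it through.** The plan states no figure to reproduce here. The check is a comparison of passages, followed by age arithmetic.

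**Premise against eligibility.** The overview says that participants are under 18 at T0. The inclusion criterion and the Abstract set a floor of 16 and no ceiling. The Ethics row requires guardian consent only if the patient is under 18, so it allows for patients who are not. The sample size section counts the centre's patients over 16 as meeting the inclusion criteria, again with no ceiling. Nothing in the article makes the premise true.

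**T0.** The labels printed in the article are 11–18 (YSR) and 6–18 (CBCL).

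- Aged 18 at T0: contradicts the premise, but is still within both labels.
- Aged 19 or over at T0: outside both labels. The share is not stated and cannot be derived.

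**T2.** Inputs: T0 to T1 is usually 6 to 18 months (Procedures); T1 to T2 is about 12 months (T2 section). The T0–T2 interval is therefore about 18 to 30 months, and

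age at T2 = age at T0 + gap/12 + 1, with the gap in months.

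Taking adult to mean 18 or over, a participant is under 18 at T2 when age at T0 < 17 − gap/12.

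| T0–T1 gap (months) | Age at T2 if 16.0 at T0 | Under 18 at T2 if T0 age is below |
|---|---|---|
| 6 | 17.5 | 16.5 |
| 9 | 17.75 | 16.25 |
| 12 | 18.0 | 16.0 (not eligible) |
| 18 | 18.5 | 15.5 (not eligible) |

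Within the usual schedule, two conditions are therefore both necessary: T0 age below 16.5 and a gap below 12 months.

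**Illustrative size at T2.** Assume T0 age uniform from 16 to 16 + w years and, independently, the gap uniform over 0.5 to 1.5 years. Put x = T0 age − 16 and y = gap − 0.5. The condition becomes x + y < 0.5, a triangle of area 0.5 × 0.5 × 0.5 = 0.125. The share is 0.125/w.

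| Assumed T0 age range | w | Under 18 at T2 | Of 90 participants |
|---|---|---|---|
| 16–17 | 1 | 12.5% | 11.3 |
| 16–18 | 2 | 6.25% | 5.6 |
| 16–19 | 3 | 4.2% | 3.8 |
| 16–20 | 4 | 3.1% | 2.8 |

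A simulation of one million draws per range gave 12.5%, 6.2%, 4.2% and 3.1%.

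Under the same ranges, the share aged 19 or over at T0 is zero for the first three and 25% for 16–20. That share is set entirely by the assumed upper age, so it is no estimate. Older T0 ages shrink the T2 problem and enlarge the T0 problem.

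**The case against.** The strongest reply is that few participants may be affected. T0 is the last visit at the child unit, so enrolment may cluster near 18. The share aged 19 or over could be small or nil, and an 18-year-old is still within the youth labels. Being under 18 at T2 is possible rather than certain, and a uniform age distribution starting at 16 has no support in the documents. All of this stands and limits the size of the point. It does not remove the conflict between the stated premise and the eligibility and consent wording.

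Nor can the point be put down to condensation for a journal. The article gives both the rule and its reason, and the reason is not assured for the patients it admits.

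Three stronger readings are tempting and should not be drawn:

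- *That the affected scores are unusable because they cannot be referred to age norms.* The article does not say that norm-referenced scores will be used; it states only a paired comparison. It also gives no numeric age range for the ASR or ABCL, so the T2 mismatch rests on their description as adult forms.
- *That the ETRC has the same fault, because it is described as exploring* "readiness for the transition process in 16–17-year-old teenagers" *yet is used at all three visits.* The article describes no adult alternative, and keeping one instrument is what a repeated-measures comparison needs. Choosing by age would change nothing there.
- *That a complete age rule for the PedsQL is ready to copy.* The overview has one, but the Measures section lists only the Teen version at T0, so those two places need aligning as well.

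**Conclusion.** The point holds as a contradiction in the rule for choosing forms. The under-18 premise is not supported by the eligibility criteria, the Abstract or the consent wording. Two groups can receive a form intended for another age group: anyone aged 19 or over at T0, in unknown number, and participants aged under 16.5 at T0 with a T0–T1 gap under 12 months. The second group is about 3% to 12.5% under the assumed uniform ages and gaps, or roughly 3 to 11 of 90. These percentages are illustrations, since the documents give no age distribution.

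The effect is limited to one secondary analysis, the paired T0–T2 comparison of YSR/ASR and CBCL/ABCL. The primary outcome and the sample size are not affected. This should be fixed, but it does not threaten the study.

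**What to change.** 1. In the Assessment tools overview and in Measures, replace the visit-based assignment with selection by the participant's age at each assessment: YSR and CBCL within their labelled range, ASR and ABCL for adults. State which pair applies at age 18, where the youth label and adulthood overlap.
2. Delete the statement that participants are under 18 at T0.
3. Align the PedsQL entry for T0 in Measures with the age-based choice in the overview.
4. Record in the case report form which behavioural form was used at each visit.
5. Report the paired T0–T2 comparison with the form combination identified (youth–youth, youth–adult, adult–adult).

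Alternatively, add an upper age limit at T0 to the inclusion criteria. That would settle only the T0 mismatch; participants enrolled soon after 16 could still receive the adult forms at T2 while under 18. It would also narrow a population from which the plan already expects only 900 × 0.13 × 0.75 ≈ 88 consenting patients, on one year's count, against a minimum of 90.

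The cost is some protocol wording and one form field. The drawback of choosing by age is that some participants will keep the same form at both visits while others switch, which is why item 5 is needed. The change should precede administration of the forms, because it cannot be made at analysis.
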